#### 11.5.1 Week 16 Visit

Patients who have not responded to treatment by achieving partial or complete remission at the week 16 visit (16 weeks from Day 0, +/- 1 week) will leave the trial and return to standard of care treatment. These patients will not receive the third dose of rituximab or placebo at week 26 as they have not demonstrated steroid responsiveness, and on-going treatment with prednisolone with or without rituximab is likely to be futile.

### 11.6 Remission Visit

The remission trial visit will:

- a. Be scheduled within two weeks of nephrotic symptoms resolving and urinalysis showing less +++ proteinuria on home or hospital testing
- b. Be taken to have occurred if blood and urine tests at a trial visit confirm remission

At the remission visit (or over a period of up to 2 weeks from resolution of nephrotic syndrome), procedures performed will be:

- Weight
- Blood pressure
- Haematology
- Biochemical analysis
- Urinary PCR
- 24 hour urine collection for proteinuria (within two weeks of remission visit)
- Concomitant medications - see section 10.3.3
- AE assessments
- Issue patients with urine dipsticks for monitoring
- Health status questionnaire: EQ-5D-5L
- Additional Health Costs questionnaire: out of pocket expenditure related to kidney, employment status, work productivity and activity impairment questionnaire, carer time
- Prednisolone dosing
- CNI dosing (if applicable)
- Immunoglobulins G and M

### 11.7 Post-remission trial visits - aligned with standard of care

Following remission, trial visits will be performed every 4 weeks (+/- 1 week) for 12 weeks, then every 3 months (+/- 2 weeks) till trial end or relapse. Procedures will be performed (over a period of up to 2 weeks) as per the remission visit:

- Weight
- Blood pressure

- Haematology
- Biochemical analysis
- Urinary PCR
- 24 hour urine collection for proteinuria (performed at Month 24 only)
- Concomitant medications - see section 10.3.3
- AE assessments
- Urine protein stick testing compliance check – only once participants have achieved complete remission
- Health status questionnaire: EQ-5D-5L
- Additional Health Costs questionnaire (performed at 12 weeks post remission & then 6 monthly)
- Prednisolone dosing
- Immunoglobulins G and M (performed every 6 months post remission)

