### 10.3.3 Concomitant therapy

Participants will continue to be treated with routine concomitant medications for other co-morbidities as appropriate within their current clinical condition, with modifications e.g. oral to IV switches, or temporary cessation as necessary. Appropriate supportive care may also be prescribed, including fluids, nutritional supplements and other medications as necessary. Other immune suppression for NS (excluding prednisolone and CNIs), e.g. mycophenolate mofetil will be stopped at randomisation.

All concomitant medications will be reviewed by local direct care team as per preferred local practice but only specified concomitant medications detailed below will be recorded in the CRF.

Prophylaxis against *Pneumocystis Jiroveci* pneumonia should be given for at least 6 months from starting trial treatment, as per local practice. It is recommended that blood pressure should be controlled to a target of < 130/80mm Hg. The use of Angiotensin Converting Enzyme inhibitors (ACEi) and Angiotensin Receptor Blockers (ARB) at the highest dose tolerated is strongly recommended and the use will be recorded.

Prophylaxis against glucocorticoid induced peptic ulceration and osteoporosis is also recommended as per local practice. Consideration should be given to performing a bone density assessment at the start of the trial and at six months to assess glucocorticoid induced bone loss.

Prophylaxis against venous thromboembolic disease is recommended in patients with serum albumin below 20g/l as per local practice.

Prophylaxis against tuberculosis is also recommended in high risk patients according to local practice.

The use of live viral vaccines during IMP treatment or while remaining B-cell depleted is not advised; should any vaccines be required during the study, it is recommended these should be completed at least 4 weeks prior to commencing the next dose of IMP.

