- Serum pregnancy test (if appropriate for female participants)
- Immunoglobulins G and M
- Urinary PCR
- Serology for hepatitis B, C and HIV
- Health status questionnaire: EQ-5D-5L
- Additional Health Costs questionnaire: out of pocket expenditure related to kidney disease over the previous 3 months, employment status, work productivity and activity impairment questionnaire, carer time
- A 24 hour urine collection for proteinuria
- Concomitant medications – see section 10.3.3
- Adverse event review
- Prednisolone dosing
- CNI dosing (if applicable)

Subsequent visit timings are based on the date of Day 0 (SPPR) i.e. when the standard prednisolone regime is started for treatment of the new onset/relapse of nephrotic syndrome, except for the post-remission assessments.

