### 11.8 **Week 24 (pre 3rd IMP dose) assessment**

For the trial patients who achieved remission within 12 weeks from SPPR an extra trial visit will be mandated within 2 weeks preceding the 26 week treatment visit (or combined with the 26 week 3rd dose treatment visit). No extra visit will be required for patients who achieved remission after 12 weeks from SPPR if a trial visit is already scheduled in the two weeks preceding IMP administration, and the procedures for both visits will be combined. These patients will be attending the standard post-remission visits schedule as detailed above.

At the trial visit performed in the 2 weeks preceding the third IMP dose administration (or combined with the 26 week 3rd dose treatment visit), both questionnaires will be completed and 24 hour urine collection containers will be handed out. Female participants must have serum or urine pregnancy test performed and continued eligibility confirmed before the third dose of IMP is given.

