| Additional Health Costs questionnaire                               |   | x |  |                                                                                                                                                                                                                                                               |   | x |   | x |   | x | x  | x | x | x | x |
| IMP administration                                                  |   |   |  | ≤4 weeks after SPPR (dose 1), repeated 2 weeks later (- 1 week or + 2 weeks allowed)(dose 2), and in week 26 (+/- 2 weeks) (dose 3) if remission by week 16 achieved and maintained. The week 24 visit could be combined with the week 26 IMP administration. |   |   |   |   |   |   |                 |   |   |   |   |
| Prednisolone dosing/ compliance                                     | x |   |  | x                                                                                                                                                                                                                                                             | x | x | x | x | x | x | x               |   | x | x | x |
| CNI dosing (if taking at entry)                                     |   |   |  | x                                                                                                                                                                                                                                                             | x | x | x |   |   |   |                 |   |   |   |   |

1. Day 0 is commencement of steroid treatment: eligibility blood and urine test results can follow. However randomisation must be after eligibility is confirmed. Day 0 (screening) and eligibility visits will be combined wherever possible, but must occur within a 4 week period if assessments performed over multiple visits.
2. Timings of treatment phase visits based on when first prednisolone dose given (SPPR). Once remission is achieved, move to post remission follow up visits
3. Please refer to section 11.12 of protocol for participant final visit timing
4. 3 monthly post-remission visit starting 3 months after the week 12 post remission visit till trial close
5. Neutrophils, Lymphocytes.
6. Urea, creatinine, e-GFR and albumin.

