7. Serum pregnancy test required for eligibility. The week 24 visit will be performed in the 2 weeks prior to administration of IMP, or the same day, and can be combined with a post remission trial visit if appropriate. Serum or urine pregnancy needs to be carried out ≤ 14 days before IMP administration in all women of child-bearing potential.
8. Participant should be withdrawn from the trial in case he/she hasn't achieved partial remission by week 16.
9. Optional dipstick testing encouraged for patients in complete remission only. See section 11.7 for further details.
10. Additional Health Cost Questionnaires performed 6 monthly in these visits.
11. AE assessments/ Con med check will be carried out in clinic visits before prescription for IMP infusion is given. They will not be checked on day of infusion unless combined with another trial visit. Trial participants withdrawn from treatment will require safety reporting (SAR/SUSAR only) for up to 12 months post last IMP dose.
12. Ig G & M done 6 monthly at these visits

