#### 16.4 Economic Evaluation

Cost-effectiveness, cost-utility and value of information analyses will be conducted from the perspectives of NHS and society over the trial duration (within-trial analysis), and over a patient lifetime (decision model-based analyses) comparing rituximab versus placebo.

Cost categories will be drugs (sourced from 'concomitant medications' measurement), secondary care contacts (sourced from HES), out of pocket costs and lost productivity accrued by the patient plus carer where applicable (patient questionnaires). The NHS perspective is defined as drugs and secondary care contacts. The societal perspective is defined as NHS plus out of pocket costs and lost productivity.

Outcome for the cost-effectiveness analysis will be adapted from the primary outcome (reported as disease and adverse event free period), and for the cost-utility analysis will be QALYs, using utilities calculated from the EQ5D5L using the recommended valuation set at the time of analysis, and integrated with respect to time.

A decision model will combine evidence from the clinical trial with other relevant evidence obtained from the literature to predict longer term costs and outcomes and hence cost-effectiveness. The model will be used to perform a value of information analysis which will predict the expected return on investment from further research into rituximab in MCD/FSGS.

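### Drug costs are to come from a medication record that omits drugs treating the trial's own adverse events of special interest, and the cost questionnaire's only stated recall period is half its later interval

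*Protocol*

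**What the plan says.** **Drugs.** Section 16.4 states: "Cost categories will be drugs (sourced from 'concomitant medications' measurement". Secondary care contacts come from HES, and out-of-pocket costs and lost productivity from patient questionnaires. The NHS perspective is drugs plus secondary care; the societal perspective adds the questionnaire items. Section 10.3.3 states that "only specified concomitant medications detailed below will be recorded in the CRF". The text below that sentence covers ACE inhibitor and ARB use, which is expressly to be recorded, and prophylaxis against pneumocystis, peptic ulcer, osteoporosis, thromboembolism and tuberculosis, with advice on blood pressure and vaccines. Prednisolone and CNI dosing have their own rows in table 11.15.

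**Questionnaire.** At screening and Day 0 (section 11.3.1) the Additional Health Costs questionnaire asks about "out of pocket expenditure related to kidney disease over the previous 3 months". At remission (section 11.6) the content is listed without a recall period: "Additional Health Costs questionnaire: out of pocket expenditure related to kidney, employment status, work productivity and activity impairment questionnaire, carer time". After remission (section 11.7) the entry reads "Additional Health Costs questionnaire (performed at 12 weeks post remission & then 6 monthly", and footnote 10 of table 11.15 agrees: "Additional Health Cost Questionnaires performed 6 monthly in these visits". Footnote 4 fixes the visits to which this refers: "3 monthly post-remission visit starting 3 months after the week 12 post remission visit till trial close". Before the third dose (section 11.8), "both questionnaires will be completed and 24 hour urine collection containers will be handed out". Table 11.15 also marks the form at month 24 and at relapse. EQ-5D-5L is completed at every 3-monthly visit.

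**The concern.** The effect on cost is the first-listed secondary objective, and both problems lie in what is collected. An analysis plan can scale or interpolate, but it cannot recover a drug that was never recorded or a month that was never asked about.

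The drug record matters more. Section 13.3.3 defines several adverse events of special interest by the need for medication: infections that need anti-infective treatment, mood change needing medication, and gastritis or ulcer needing medication or endoscopy. It also lists new-onset diabetes. These are drug costs that rituximab or steroid exposure could change. Section 16.4 adapts the effectiveness outcome into a period free of both disease and adverse events. An adverse event can therefore reduce measured benefit while the drug that treats it is missing from measured cost.

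For the questionnaire, the later interval is twice the only recall period in the protocol, so under that recall half of each 6-month interval would not be asked about.

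**Working it through.** **1. Drug record: sections set side by side.**

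| Drug group | Recorded as the protocol is written? |
|---|---|
| Prednisolone, CNI | Yes, own rows in table 11.15 |
| ACE inhibitor, ARB | Yes, section 10.3.3 |
| Prophylaxis named in 10.3.3 | Apparently, as medicines detailed there |
| Anti-infective treatment | Not named |
| Drugs for new diabetes, mood change, gastritis | Not named |

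The adverse events themselves go into the CRF (sections 13.3.3 and 13.4.4), and hospital contacts for them reach the analysis through HES. The component with no stated source is drugs given outside hospital for these events. No recall assumption is needed for this part.

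**2. Questionnaire coverage in continued remission.** The protocol gives no coverage figure to reproduce. Inputs: forms at remission, 12 weeks later, week 24, then every 6 months after the 12-week form, and month 24. Assumptions: each form covers the preceding 3 months; 1 week = 12/52.1775 months.

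Example, remission at week 4. Forms fall at months 0.9, 3.7, 5.5, 9.7, 15.7, 21.7 and 24. The covered stretches are months 0–5.5, 6.7–9.7, 12.7–15.7 and 18.7–24, so coverage is 5.5 + 3.0 + 3.0 + 5.3 = 16.8 months, and 16.8/24 = 70%.

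| Remission at week | Covered months of 24 | Share |
|---|---|---|
| 4 | 16.8 | 70% |
| 8 | 15.9 | 66% |
| 12 | 15.0 | 62.5% |
| 16 | 14.8 | 62% |

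Under other recall periods, coverage is 23–29% (1 month) or 100% (6 months). Beyond month 24, 3-month recall every 6 months covers 3/6 = 50%.

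**3. By arm.** Section 16.2 assumes median times to relapse of 9 and 18 months. As a check on these inputs, with λ = ln 2/median, 30 months of uniform accrual and 24 further months, P(event) = 1 − (e^(−24λ) − e^(−54λ))/(30λ) = 0.939 and 0.765. Then 39 × (0.939 + 0.765) = 66.4 events from 78 patients, against 67 stated.

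Exponential relapse times were simulated (4,000 per arm), with remission at week 4, 8 or 12, 3-month recall, a form at relapse, and no open label data:

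| Per remitter, to month 24 | Control | Rituximab |
|---|---|---|
| Months in main phase | 11.7–13.2 | 16.3–17.3 |
| Of these, not covered | 2.4–3.5 | 4.1–5.5 |
| Share of main-phase time covered | 74–80% | 68–75% |
| Months after relapse | 10.8–12.3 | 6.7–7.7 |
| Share of all 24 months covered | 39–41% | 49–51% |

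The gap while in the trial is 1.7–2.0 months longer on rituximab (4.1 − 2.4; 4.7 − 2.9; 5.5 − 3.5). Counted over the full 24 months, control has the lower coverage.

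**The case against.** The strongest objection is to the questionnaire point. The 3-month recall is written once, for the baseline form, where a fixed look-back is natural, and it attaches to out-of-pocket spending, not to employment, work productivity or carer time. The follow-up form is not in the protocol. If it asks about the time since the previous form, the gap disappears. Even with a fixed window, blanks understate cost only if they are counted as zero, and the method of scaling may be in an analysis plan not shown. All of this stands, so the 62–70% is conditional. What remains is that the protocol leaves the follow-up recall unstated beside an interval twice the only one it gives.

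Against the drug point it can be said that hospital contacts are costed from HES, that the adverse events are in the CRF and so can be identified, and that prednisolone and CNI doses do not depend on the restricted list. This also stands. A reader might infer that the cost of treating harms is left out of the NHS perspective altogether; HES rules that out. It does not supply a stated source for drugs given outside hospital.

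A reader might also infer that costs are understated most in the arm that stays longer in remission, to rituximab's advantage. The documents do not support this. Main-phase collection also ends at relapse and at week 16 without remission (sections 11.5.1 and 11.12). Relapse is expected more often in control, which reverses the order of total coverage unless open label data are used. The protocol gives no cost for a month in remission, and nothing ties the restricted drug list to one arm.

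**Conclusion.** The drug point holds on the text alone: followed as written, sections 10.3.3 and 16.4 leave drugs given outside hospital for the protocol's own adverse events of special interest without a stated cost source. The drug component of the NHS perspective is incomplete. The documents give no prices or event rates, so its monetary size cannot be stated.

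The questionnaire point is secondary and conditional. If the Day 0 recall applies throughout, about 62–70% of the time is covered for a patient in remission to month 24, and half of any later time. If the follow-up form asks about the whole interval, only a clarification is needed.

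No direction of bias between the arms is claimed. The arm figures rest on exponential relapse at the section 16.2 medians. The net direction depends on open label uptake and on whether those costs enter the comparison, neither of which the protocol states.

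**What to change.** In section 10.3.3, replace the loosely defined set of specified medicines with an explicit list of what is recorded for costing. Add to it all drugs given for nephrotic syndrome and all drugs given to treat an AESI or SAE, so that section 16.4 can cost them. This is a recording change only, at the cost of a few extra CRF lines.

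In sections 11.6 and 11.7 and table 11.15 (footnote 10), state the follow-up recall period and match it to the interval. One option is to ask about the time since the previous form, which adds no forms, closes the gap and avoids overlap among the early forms, but lengthens recall to 6 months in stable remission. The other is to give the 3-month form at every existing 3-monthly visit, which closes the gap apart from visit windows and adds a short form at visits that now have none. Neither option needs a new visit, and neither recovers costs after relapse or week-16 exit.

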### 11.8 **Week 24 (pre 3rd IMP dose) assessment**

For the trial patients who achieved remission within 12 weeks from SPPR an extra trial visit will be mandated within 2 weeks preceding the 26 week treatment visit (or combined with the 26 week 3rd dose treatment visit). No extra visit will be required for patients who achieved remission after 12 weeks from SPPR if a trial visit is already scheduled in the two weeks preceding IMP administration, and the procedures for both visits will be combined. These patients will be attending the standard post-remission visits schedule as detailed above.

At the trial visit performed in the 2 weeks preceding the third IMP dose administration (or combined with the 26 week 3rd dose treatment visit), both questionnaires will be completed and 24 hour urine collection containers will be handed out. Female participants must have serum or urine pregnancy test performed and continued eligibility confirmed before the third dose of IMP is given.

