### 11.9 **Third dose of treatment**

Patients in remission will receive the third dose of IMP at 26 weeks (+/- 2 weeks). No additional trial assessments will be mandated at this visit as patients will have had a trial visit in the preceding two weeks (unless it is combined with Week 24 (pre 3rd IMP dose) assessment as above)

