#### 11.13 **Open label phase visits (See table 11.15)**

Participants who have achieved remission by week 16 and gone on to meet the primary endpoint of relapse will be unblinded by the local PI or a delegated member of the trial team (sub-investigator/associate PI) in a restricted fashion. This is to determine eligibility for the OLP. Consent for the OLP will be optional and will be sought from participants at entry to the main trial. Once participants have relapsed and become eligible for the OLP, a currently REC and or MHRA approved version of consent form must be signed by participant to confirm their

informed consent. The delegated clinician must confirm that there has been no change in clinical condition of the trial participants that could preclude rituximab treatment. A serum/urine pregnancy test must be performed before rituximab infusions can be given (if appropriate). The negative pregnancy test should be confirmed only at the local site and not communicated to central coordination team via CRF to preserve the blind.

Participants who are eligible to go into the OLP will be required to attend 3 research visits to receive rituximab infusions. AE and concomitant medication reviews will take place at standard of care clinic visits which will precede these infusion visits. Follow up visits and procedures will be performed at the same time points as during the RCT phase of the trial, with blood and urine results collected as per local clinical care guidelines and supplemented with data collected via RaDaR at the end of the trial. Protocolised prednisolone regimen has to be selected at OLP initiation and followed as per protocol. This regimen can be different to regimen previously tried in main trial. The date of restarting high dose steroids is taken as Day 0 in the OLP. Additional Health Costs questionnaire (out of pocket expenditure related to kidney, employment status, work productivity and activity impairment questionnaire, carer time) to assess impact of kidney disease on costs and productivity and EQ-5D-5L will also be completed as per the visit schedule for the RCT phase of the trial. As in the RCT phase, the third dose of rituximab at 26 weeks will not be administered if the patient does not achieve at least partial remission sustained to 26 weeks.

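### Dose 3 requires maintained remission, but the mandated pre-dose-3 visit schedules no urinary PCR or albumin, so early remitters are dosed on a PCR nominally 6 to 10 weeks old

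*Protocol*

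**What the plan says.** **The dosing condition.** Protocol 11.9 states: "Patients in remission will receive the third dose of IMP at 26 weeks". The IMP administration row of table 11.15 allows dose 3 "if remission by week 16 achieved and maintained". Section 11.13, describing the open-label phase as following the randomised phase, says that the third dose "will not be administered if the patient does not achieve at least partial remission sustained to 26 weeks". Section 10.1.7 is looser: it asks only for remission by week 16.

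**How remission and relapse are measured.** Under 8.6.1 and 14.1, complete and partial remission are defined by urinary PCR. Relapse needs PCR above 300 mg/mmol, a doubling from the nadir and albumin below 35 g/l.

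**The visit before dose 3.** For participants who remit within 12 weeks of Day 0, 11.8 mandates an extra visit in the two weeks before the dose. At that visit "both questionnaires will be completed and 24 hour urine collection containers will be handed out". Women also need a pregnancy test and "continued eligibility confirmed before the third dose of IMP is given"; no laboratory test is attached to that check. In table 11.15 the Week 24 column is marked for pregnancy test, 24-hour urine, concomitant medications, adverse events and both questionnaires. It is blank for urinary PCR and for biochemistry, which is where albumin sits. Footnote 7 allows the visit on the infusion day: "The week 24 visit will be performed in the 2 weeks prior to administration of IMP, or the same day".

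**The dosing visit.** Section 11.9 adds nothing: "No additional trial assessments will be mandated at this visit as patients will have had a trial visit in the preceding two weeks".

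**The concern.** Section 11.9 relies on the preceding visit to have settled whether the participant may be dosed, but that visit does not schedule the two tests that define the answer. The 24-hour collection does not fill the gap. The container is only handed out at a visit that may fall on the infusion day, so no result is required before dosing, and the collection gives no albumin.

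What is at stake is the dosing rule. A participant who has relapsed without anyone noticing could receive a third infusion that the protocol intends to withhold. Participants in partial remission are least protected, because 11.11 excludes them from dipstick monitoring. The timing is also unhelpful. Under Regimen 1 (10.3.1) the taper runs 16 weeks (six 2-week steps from 40 mg to 10 mg, then two 2-week steps at 5 mg) and starts at most 2 weeks after remission. A week-4 remitter who stops prednisolone therefore does so at about weeks 20 to 22, after the last scheduled PCR at week 16 and before dose 3. Section 6.2.1 describes steroid reduction or withdrawal as the setting in which relapses occur.

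**Working it through.** **1. Age of the last scheduled PCR at dose 3.** By 11.7 and footnote 4 of table 11.15, a participant remitting at week r has PCR and biochemistry at r+4, r+8 and r+12 (each ± 1 week), then 3 months after r+12, at about r+25. Dose 3 is at week 26 ± 2 (10.1.7). For remission up to week 12, the age at a week-26 dose is 26 − (r+12) = 14 − r.

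| Remission week | Last scheduled PCR | Age at week 26 | Next scheduled PCR |
|---|---|---|---|
| 4 | week 16 | 10 weeks | about week 29 |
| 8 | week 20 | 6 weeks | about week 33 |
| 12 | week 24 | 2 weeks | about week 37 |

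- With the visit and dose windows, the ages are 7 to 13 weeks (r = 4) and 3 to 9 weeks (r = 8). One exception: for r = 4, a 3-monthly visit held two weeks early (week 27) could precede a dose at week 27 or 28.
- Section 14.2 can be read as 3-monthly from the remission date. That adds a PCR at about r+13, and the ages become about 9 and 5 weeks.
- For remission at week 14 or 16 the nominal age is 0 or 2 weeks. The gap is confined to earlier remitters.

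**2. Chance of any relapse between the last scheduled PCR and week 24.** Inputs are the medians in 16.2: 9 months (control) and 18 months (rituximab), taken as exponential. Check against Appendix 5, in six-month periods: 0.5^(1/1.5) = 0.630 and 0.5^(1/3) = 0.794, which match its first-period survival values.

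P = 1 − exp(−ln 2 / median × (12 − r)/4.345), for someone still in remission at r+12:

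- r = 4 (8 weeks): 0.132 control, 0.068 rituximab.
- r = 8 (4 weeks): 0.068 control, 0.035 rituximab.

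Probability of still being in remission at r+12: exp(−ln 2 / median × 12/4.345) = 0.81 control, 0.90 rituximab.

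**3. Expected participants with an unrecognised relapse.** Responders per arm are 75% (16.2) of 65 to 75, or 48.75 to 56.25. The protocol gives neither the timing of remission nor the share of relapses that would go unnoticed. Assumed: 25–50% of responders remit at week 4, 25% at week 8, and 10–50% of relapses are unrecognised.

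- Low (25%/25%, 10%): control 48.75 × (0.25 × 0.132 + 0.25 × 0.068) = 2.45; × 0.81 × 0.1 = 0.2. Rituximab 1.26 × 0.90 × 0.1 = 0.1.
- High (50%/25%, 50%): control 56.25 × (0.50 × 0.132 + 0.25 × 0.068) = 4.68; × 0.81 × 0.5 = 1.9. Rituximab 2.41 × 0.90 × 0.5 = 1.1.

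The constant hazard could understate risk just after steroids stop; the 50% upper share probably overstates how many relapses of nephrotic syndrome would be missed.

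**4. After the change.** With PCR and albumin taken in the two weeks before the dose, the last result is at most 2 weeks old for every remission date.

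**The case against.** The protocol sets a condition and leaves the investigator to confirm it. Since remission is defined by PCR, a careful clinician would order one, and 14.2 permits extra assessments when clinically indicated. There are other checks: adverse-event and medication review before the prescription (table 11.15, footnote 11: "Con med check will be carried out in clinic visits before prescription for IMP infusion is given"), patient reporting of oedema, and weekly dipsticks in complete remission. The synopsis lists the week-26 items within its post-remission row, where PCR and biochemistry carry no time restriction, although the row's stated schedule is 4-weekly for 12 weeks and then 3-monthly. All this stands as mitigation and explains why the expected number is small. None of it requires a PCR or albumin result before dose 3.

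Another fair point concerns the remedy. Relapse tests now run on the remission clock. A test tied to Day 0 would fall at about r+20 for week-4 remitters and r+16 for week-8 remitters, while adding nothing for week-12 remitters. If rituximab changes time to remission, the intensity of relapse checking would differ slightly between arms. This is a small cost, but it should be stated.

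Stronger readings do not hold. A reader might infer that the primary endpoint is compromised. The schedule is the same in both arms, relapse is still assessed at the 3-monthly visits and on symptoms, and the placebo infusion is saline. A reader might also extend the point to the open-label phase. There, laboratory results follow local care (11.13) and the data do not contribute to main-phase efficacy or safety (10.2), so no main-phase result is at risk.

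**Conclusion.** The point holds as a cheap improvement to the main-phase visit schedule. The dosing condition for dose 3 is not checked by any scheduled PCR or albumin close to the dose for participants who remit early: the nominal PCR age is 10 weeks for remission at week 4 and 6 weeks for week 8 (about 9 and 5 on the 14.2 reading). These ages follow directly from the schedule.

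The participant counts in step 3 are less secure. They rest on exponential relapse at the planning medians and on assumed shares for remission timing and unrecognised relapse that the protocol does not supply. They show an order of magnitude: around one rituximab participant at the most, on the high assumptions.

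Someone might read the looser wording of 10.1.7 as permission to dose after relapse. Section 11.9 and table 11.15 both require current remission, so this is a wording mismatch and not a second dosing rule.

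**What to change.** - Add urinary PCR and biochemistry (albumin) to the list in 11.8 and to the Week 24 column of table 11.15. Take them within 2 weeks before dose 3, with results reviewed before the dose is released.
- Add *and maintained* to 10.1.7, to agree with table 11.15.
- State that the purpose is to confirm the dosing condition. A relapse found this way is confirmed and dated under the existing definition, like any unscheduled assessment under 14.2.
- Matching table 11.16 for the open-label phase is optional.

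**Cost.** One spot urine and one routine blood sample at a visit already mandated, plus amendment wording. Where the visit is combined with the infusion, samples must be taken a few days earlier; any short wait for results fits the ± 2 week dose window. Early remitters gain one additional relapse check tied to Day 0.
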